## Abstract

**Background:**

Up to 25–35% of women receive antibiotics (ABX) during pregnancy, but little is known about the consequences on a key mucosal interface such as the mammary gland, and on the development of the neonatal gut’s microbiota and IgA. We hypothesize that prenatal ABX negatively affect the immune functionality of mammary gland, the composition of breast milk microbiota, the development of neonatal fecal microbiota and the abundance of neonatal fecal IgA.

**Methods:**

Case-control translational cohort study on women and neonates in the presence or absence (*N* = 41 + 41 pairs) of exposure to prenatal ABX for at least 7 consecutive days after 32 weeks of gestation.

**Results:**

We will evaluate IgA concentration in breast milk and in neonatal feces up to one year after delivery. We will also evaluate clinical parameters, neurodevelopment and the composition of the IgA-coated and uncoated fractions of breast milk and fecal microbiota by means of magnetic-activated cell sorting (MACS) coupled with shotgun metagenomics. Finally, we will measure the concentration of the chemokine CCL28 on maternal serum and breast milk, as a marker of activity of the entero-mammary pathway.

**Conclusions:**

Our results might support a data-driven evaluation of breast milk immune function in women exposed to prenatal ABX.

**Impact:**

Breast milk IgA and microbiota are critical to determine the positive effects of breastfeeding in infants.This research protocol will investigate breast milk IgA, microbiota, and the IgA^+^ / IgA^−^ fractions of neonatal fecal microbiota upon exposure to prenatal antibiotics.Fecal IgA and microbiota in infants exposed or not exposed to prenatal antibiotics will be analyzed up to 1 year after birth.This research will clarify the impact of prenatal antibiotics on the immune function of breast milk.This, in turn, might support the selective evaluation of breast milk IgA/microbiota in mothers exposed to prenatal antibiotics, or in donor human milk.

## Introduction

At the mucosal sites of human body, the relationship between the microbiota and the immune system is mutual: the abundance and diversity of microbiome can affect the function of immune system, while the components of the mucosal immune system, such as secretory IgAs (sIgA), can in turn shape the microbiota composition.^1–5^ Indeed, it is known that humans deficient in IgA have a unique intestinal microbiota characterized by the expanded of *Enterobacteriaceae*,^6^ akin to IgA-deficient murine strains where *Enterobacteriaceae and* segmented filamentous bacteria (SFB) are predominant.^7,8^ In early life, breast milk microbiota and breast milk immune components, such as lactoferrin and sIgA excreted by the mammary gland plasma cells, play key roles in shaping the assembly of neonatal intestinal microbiota and contribute to the passive protection of neonates against bacterial translocation from the gut.^3,9–11^ The positive effects of breast milk on infants’ health might not be limited to the gut health or to the breastfeeding period: a growing body of evidence reveals that breastfeeding probably has a positive influence on neurodevelopmental long-term outcomes compared to formula feeding in both term-^12,13^ and preterm-born children,^14^ and on the body composition and growth of children even beyond the breastfeeding window.^15,16^ These effects might be largely contributed by the unique intestinal microbiota induced by breastfeeding, and by the immune components of breast milk themselves.^17,18^

Antibiotic (ABX)-induced dysbiosis is known to disrupt the immune function of different mucosal sites, such as the gut and the lungs of adult individuals,^19^ but the effect on the mammary gland immune system is not known. Moreover, ABX administered directly to neonates during the first days of life are also known to induce neonatal dysbiosis and are associated with short- and long-term immune-related adverse outcomes such as an increased incidence of necrotizing enterocolitis (NEC), atopy, and obesity.^20–22^ Despite such an extensive knowledge on the effects of postnatal ABX, the effect of prenatal ABX-induced dysbiosis on the breast milk immune function and on the development of mucosal neonatal immune system is poorly understood. Our recently published data on a murine model of prenatal ABX exposure showed that maternally administered ABX during the last week of pregnancy decrease both maternal and neonatal mucosal IgA and induces a long-term derangement of neonatal fecal microbiota.^23^ A recent, not peer-reviewed work confirmed our findings.^24^ We hypothesize that prolonged ABX therapy (≥7 days of therapy) administered to pregnant mothers during the last stage of pregnancy, i.e., shortly before birth, can reduce the absolute amount and the polyreactivity of breast milk IgA after birth, even without any administration of ABX during the breastfeeding period. This reduction could be caused by an impaired functionality of the so-called “entero-mammary pathway”, through which plasma cells migrate to the mammary gland from the mesenteric lymph nodes driven by the gradient of the epithelial chemokine CCL28 produced by the mammary gland itself.^25^ Therefore, we hypothesize that maternal intestinal dysbiosis during the last stages of pregnancy can impair the migration of IgA-producing plasma cells to the mammary gland. Moreover, most prescribed ABX in obstetric clinical practice, such as penicillins and macrolides, are easily absorbed and can diffuse in all body tissues. We thus hypothesize that breast milk microbiota itself might be profoundly altered by prenatal ABX.

Finally, during the breastfeeding window plasma cells of the neonatal intestinal mucosa produce limited amounts of IgA, and the concentration of fecal IgA in neonates depends almost exclusively on the passive transmission of maternal IgA through breast milk.^26^ Similarly, the composition of neonatal intestinal microbiota is greatly dependent on the type of milk received (breast milk or formula milk). We thus also hypothesize that the reduction in breast milk IgA and the alteration of breast milk microbiota induced by prenatal ABX can cause a reduction in neonatal fecal IgA, and a condition of neonatal intestinal dysbiosis favored by microbially-altered maternal breast milk.

## Methods/design

### Study design

The overall study design is summarized in Fig. 1. The study will be performed at the Department of Woman, Child and Newborn of Fondazione IRCCS Ca’ Granda—Ospedale Maggiore Policlinico of Milan, Italy, with the experimental collaboration of the Mucosal Immunology and Microbiota laboratory of IRCCS Istituto Clinico Humanitas, Rozzano (Milan), Italy. The protocol has been registered at ClinicalTrials.gov, trial code: NCT05813184. Registered on April 14, 2023. This will be a prospective case-control study enrolling pregnant women between 18 and 40 years of age exposed to antibiotic therapy during the last month of pregnancy, for a period of at least 7 days consecutively, and their newborns.

**Fig. 1 Fig1:**
[figure not shown]
Graphical overview of the study protocol and procedures. ASQ: Ages and Stages Questionnaires. CCL28: Chemokine (C-C motif) ligand 28.

Conditions for which women will be treated with prolonged antibiotics will include but will not be limited to prelabor or preterm-prelabor rupture of membranes (PROM or pPROM), preterm labor with or without PROM, urinary tract infections, clinical chorioamnionitis, pneumonia. An equal number of women and their neonates not exposed to prenatal antibiotics (any exposure during pregnancy) will be enrolled as controls. Case-control dyads will be matched for gestational age at delivery and at the start of antimicrobial treatment.

Inclusion criteria will be the expression of written informed consent by parents of the neonate, a maternal antibiotic treatment (any molecule) for at least 7 days consecutively after 32 weeks of gestational age (or the absence of exposure to any systemic antibiotic treatment during pregnancy for the control group), and the intention to breastfeed neonates as long as possible during the first year of life. Exclusion criteria will be the absence of written informed consent, the intention or medical need to formula feed exclusively (or the presence of significant maternal concerns about breastfeeding), a maternal antibiotic treatment shorter than 7 days, the presence of pre-existing maternal immune-mediated disorders (including chronic immunodeficiencies), a delivery at a gestational age <34 weeks and the administration of antibiotics to neonates after birth, within the first week of life.

The amount of IgA (in breast milk and neonatal feces), the composition of microbiota (in breast milk and neonatal feces), the proportion and profile of IgA-coated bacteria (in neonatal feces), and the concentration of the Chemokine (C-C motif) ligand 28 (CCL28, in maternal serum and breast milk) will be quantified after collection of samples during pre-planned study visits, at the following time points:during the first week of lifeat 1 month of lifeat 3 months of life

at 8–12 months of life (or at the time of breastfeeding interruption), after the introduction of solid food in the infant’s diet. At the same timepoint, five domains (communication, fine motor, gross motor, problem-solving ability, and personal-social functioning) of infants’ neurodevelopment will be assessed through the administration of Ages and Stages Questionnaire-3 (ASQ-3), and infants’ growth will be evaluated (weight, length, head circumference). The research protocol was reviewed and approved by Comitato Etico Milano Area 2, Approval number 0007973. Written informed consent will be obtained from enrolled women and the fathers of enrolled neonates. The study protocol adheres to the STROBE checklist for case-control studies and was registered at ClinicalTrials.gov (protocol code: NCT05813184, registered on April 14, 2023).

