### Data collection, sample size and statistical analysis

Demographic and clinical data will be collected prospectively in an electronic database (Excel software, Microsoft Corp.), where enrolled patients will be de-identified and associated with a single numerical code. The database will be stored on the Institutional server and encrypted according to standard internal protocols for data protection.

According to internal historical data, an average of 1.5 women per week is expected to receive prolonged ABX therapy immediately before delivery at the study site. Based on preliminary animal data, an average drop of approximately 30% in breast milk IgA can be expected after prenatal ABX treatment. Considered an average content of IgA of 3.8 g/L (S.D. ± 1 g/L), a sample size of around 34 women per group would be enough to detect a prudential difference of 20% with a power of 0.9 and an Alpha equal to 0.05. We would like to account for a dropout rate of 20%. Therefore, a sample size of 41 women per group (ABX-treated vs. controls) would be appropriate and feasible within one year in our clinical context.

Results will be represented using box plots showing the interquartile range, with a single data point per subject. Statistically significant differences between two groups will be evaluated with Mann-Whitney two-sided unpaired U-test, for non-normally distributed data (visually checked), or two-sided unpaired *t*-test for normally distributed data. In case of longitudinal experiments (e.g., IgA concentration over time in the same subjects), repeated-measures ANOVA will be applied. A probability value of **p* < 0.05 will be considered as significant. Data analysis and graphing will be performed using GraphPad Prism (GraphPad software) vers. 9.0.1, and StataMP vers. 17.0 (Stata Corp.).

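### Groups are matched on gestational age, but the named tests use neither matching nor gestational age, and one of the two matching factors has no value for controls

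*Protocol article*

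**What the plan says.** All references are to the protocol article.

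- **Matching** (Study design, text after Fig. 1): "Case-control dyads will be matched for gestational age at delivery and at the start of antimicrobial treatment". No caliper is given, and the text does not say whether matching is one-to-one or by frequency.
- **Ratio** (same section): "An equal number of women and their neonates not exposed to prenatal antibiotics (any exposure during pregnancy) will be enrolled as controls".
- **Control definition** (same section, inclusion criteria): "the absence of exposure to any systemic antibiotic treatment during pregnancy for the control group".
- **Two-group comparisons** (Data collection, sample size and statistical analysis): "Statistically significant differences between two groups will be evaluated with Mann-Whitney two-sided unpaired U-test" for non-normal data, and "two-sided unpaired *t*-test for normally distributed data".
- **Longitudinal data** (same section): "repeated-measures ANOVA will be applied". No matched-set term or gestational-age covariate is named.
- **Sample size** (same section): two independent groups, mean breast milk IgA 3.8 g/L, SD 1 g/L, a 20% difference, power 0.9, alpha 0.05. This gives around 34 per group, raised to 41 for 20% dropout.
- **Purpose of the design** (Discussion and conclusions): better control and balance of the two populations on variables such as gestational age and breastfeeding rates. No gain in precision is claimed.

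**The concern.** The analysis as stated does not follow from the design as stated. Matching on a prognostic factor makes the two groups more alike than independent samples would be, so the difference in means varies less from study to study. An unpaired test does not see this and reports a standard error that is too large. In a small study with costly laboratory work, that would waste precision already paid for through the effort of matching.

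The matching rule also has a gap. A woman never treated with antibiotics in pregnancy has no gestational age at the start of treatment, and the article gives no index date in its place. As written, that half of the rule cannot be applied to a control.

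**Working it through.** **1. The plan's own figure.** The difference is 0.20 × 3.8 = 0.76 g/L with SD 1. For two independent groups, two-sided alpha 0.05 and power 0.90:

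n = 2 × (1.960 + 1.282)² / 0.76² = 36.4, so 37 per group (38 with the exact t-test).

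The stated 34 is not reproduced. At 34 per group the t-test has power 0.87. Rounding 0.76 up to 0.8 gives 33 to 34, a possible but unstated origin. This is a separate matter from the matching. It matters here only because the formula treats the groups as independent and because there is little power to spare.

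**2. Effect of ignoring the matching.** Let ρ be the within-pair correlation of the outcome. The true variance of the difference in means is 2σ²(1 − ρ)/n; the unpaired test uses 2σ²/n. Its standard error is therefore too large by a factor 1/√(1 − ρ), and its true type I error is approximately 2 × [1 − Φ(1.96/√(1 − ρ))]:

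- ρ = 0.04: 1.96/0.980 = 2.00, type I error 0.045
- ρ = 0.3: 1.96/0.837 = 2.34, type I error 0.019

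**3. Which values of ρ are plausible.** The article gives none, so a range has to be assumed. If pairs are alike only through gestational age, ρ is at most r², where r is the correlation of the outcome with gestational age. So r = 0.2 gives ρ = 0.04 and r = 0.3 gives ρ = 0.09, while ρ = 0.3 needs r of about 0.55. Deliveries before 34 weeks are excluded, which narrows the range of gestational age and makes high values of r less likely.

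**4. Power with 34 complete pairs, difference 0.76, SD 1** (unpaired test simulated on correlated pairs; paired t-test exact):

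| ρ (assumed) | Unpaired type I error | Unpaired power | Paired power |
|---|---|---|---|
| 0 | 0.050 | 0.872 | 0.860 |
| 0.04 | 0.045 | 0.875 | 0.874 |
| 0.1 | 0.039 | 0.884 | 0.894 |
| 0.2 | 0.029 | 0.897 | 0.925 |
| 0.3 | 0.020 | 0.911 | 0.953 |
| 0.5 | 0.007 | 0.942 | 0.990 |

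With 33 pairs (41 × 0.8 = 32.8), the gap at ρ = 0.3 is 0.900 against 0.947, about 5 points.

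**5. Effect of dropout on a strict paired test.** If the two members of a pair drop out independently at 20%, 41 × 0.8² = 26.2, so about 26 complete pairs remain. Paired power is then 0.75, 0.84 and 0.88 at ρ = 0, 0.2 and 0.3. In simulations with the same dropout, the unpaired test on everyone remaining has 0.86, 0.88 and 0.89. Over this range the strict paired test does no better than the plan, and mostly worse.

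**6. A model that keeps unpaired members.** Under the same dropout, a generalised least squares stand-in for the random-pair model (without the covariate) had power 0.86, 0.88, 0.90 and 0.92 at ρ = 0, 0.1, 0.2 and 0.3, against 0.86, 0.87, 0.88 and 0.88 to 0.89 unpaired. Its type I error was 0.051 to 0.059, highest at ρ = 0.

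**7. The second matching factor.** Set the matching rule beside the control definition: the first needs a treatment start, the second rules one out. If the intended meaning is that the control was still pregnant and untreated at the age when the case began treatment, then matching on age at delivery plus the control definition already ensures it. As written, the factor is either undefined or redundant.

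**The case against.** The strongest reply is that the article never says the matching is individual. Timing of analysis uses the word dyad for mother and infant, and the stated purpose, balancing the populations, fits frequency matching equally well. Under frequency matching there are no pairs to ignore. This stands in part. One-to-one pairs are the natural reading of case-control dyads with equal numbers, but that is not stated. It does not remove the point, because under frequency matching one would still expect adjustment for gestational age, and none is named.

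The second reply is that the loss is small and rests on an assumed correlation. This stands. At correlations of 0.04 to 0.09 the gain is nil to about one point.

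A reader might go further and infer any of three things, none of which the document supports:

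- **That the matching cannot be done at all.** Gestational age at delivery exists for every woman and can be matched; only the second factor fails.
- **That the benefit of matching is thrown away.** Unpaired power itself rises with the correlation, from 0.872 to 0.911 between ρ = 0 and 0.3. Only part of the gain is forgone.
- **That the results would be biased or false positives more frequent.** With positive correlation the error goes the other way: the test is conservative.

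The article may also condense a fuller protocol that defines an index date. That would excuse a missing detail. It does not excuse naming unpaired tests for a matched design, which is a stated choice.

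**Conclusion.** The point holds in a limited form. The stated analysis ignores the stated matching, and one matching factor is undefined for controls.

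If gestational age is prognostic, the unpaired standard errors are too wide. For a within-pair correlation of 0.04 to 0.3, type I error is about 0.045 to 0.02 and roughly 0 to 5 points of power are forgone. Near zero correlation nothing is lost.

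These sizes rest on an assumed correlation, on the plan's difference of 0.76 g/L and SD of 1 g/L, and on 33 to 34 complete one-to-one pairs. The mismatch between design and analysis, and the missing control value, rest on the text alone. This should be corrected, but it does not threaten the validity of the comparison.

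**What to change.** - State whether matching is individual or by frequency.
- Drop gestational age at treatment start as a matching factor, or define it for each control as an index gestational age taken from the matched case.
- If matching is individual, record a matched-set identifier at enrolment, since pairs may not be recoverable later.
- Replace the unpaired tests for the main comparison with a linear mixed model that has gestational age at delivery as covariate and, if matching is individual, a random intercept for the pair. Carry the same terms into the longitudinal analysis. This keeps dyads whose partner drops out.
- Do not substitute a strict paired t-test or signed-rank test, for the dropout reason shown above.

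The cost is a few sentences and one database field. If the matching turns out uninformative, the loss of precision is negligible. Given the slightly raised type I error near zero correlation in step 6, a small-sample degrees-of-freedom correction is sensible. Skewed outcomes, which the plan now sends to the Mann-Whitney test, would need a transformation such as the logarithm.

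### Antibiotic courses before 32 weeks can occur only in the exposed group, so a difference in IgA cannot be attributed cleanly to exposure shortly before birth

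*Protocol article*

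**What the plan says.** All the relevant rules are in the Study design section of the protocol article.

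- **Controls.** The whole pregnancy must be free of systemic antibiotics. This is said twice: mothers and neonates "not exposed to prenatal antibiotics (any exposure during pregnancy) will be enrolled as controls", and, in the inclusion criteria, "or the absence of exposure to any systemic antibiotic treatment during pregnancy for the control group".
- **Exposed women.** The inclusion criterion is "a maternal antibiotic treatment (any molecule) for at least 7 days consecutively after 32 weeks of gestational age". The opening paragraph of the section describes them as "exposed to antibiotic therapy during the last month of pregnancy, for a period of at least 7 days consecutively". Neither wording mentions courses given earlier in the pregnancy.
- **Exclusion.** The only exclusion about maternal antibiotics is "a maternal antibiotic treatment shorter than 7 days", with no gestational window.
- **Matching.** "Case-control dyads will be matched for gestational age at delivery and at the start of antimicrobial treatment". Earlier antibiotic history is not a matching factor.

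The Introduction places the hypothesised effect in time: prolonged therapy "administered to pregnant mothers during the last stage of pregnancy, i.e., shortly before birth". The Abstract gives one figure for background use: "Up to 25–35% of women receive antibiotics (ABX) during pregnancy".

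**The concern.** The look-back period differs between the groups. A woman treated at, say, 20 weeks is barred as a control but can enter as an exposed woman if she also has a qualifying course after 32 weeks. Any first- or second-trimester exposure in the study must therefore sit in the exposed group.

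Timing is part of the hypothesis. The proposed mechanism is maternal dysbiosis late in pregnancy that impairs the entero-mammary pathway. If earlier or cumulative courses also lower milk IgA or alter the microbiota, their effect adds to the observed difference and would be read as an effect of late exposure. If earlier courses reduce IgA, the bias favours the study's hypothesis.

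**Working it through.** **Step 1: the rules side by side, before 32 weeks.**

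| Earlier course | Control | Exposed, exclusion read as the qualifying (index) course | Exposed, exclusion read as any course |
|---|---|---|---|
| None | eligible | eligible | eligible |
| Shorter than 7 days | not eligible | eligible | not eligible |
| 7 days or longer | not eligible | eligible | eligible |

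Under both readings of the exclusion, an earlier course of 7 days or longer is possible in the exposed group and impossible among controls. The two readings also enrol different women.

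**Step 2: can an analysis separate the two effects?** The share of controls with an earlier course is zero by rule. Early and late effects can be separated only by comparing exposed women with and without an earlier course, which requires that earlier courses be recorded.

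**Step 3: inputs for an illustration.**

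- From the sample-size section: mean milk IgA 3.8 g/L, SD 1 g/L, design difference 20%, two-sided alpha 0.05, 41 women per group, 20% dropout.
- The plan's target difference is 0.20 × 3.8 = 0.76 g/L. Evaluable women after dropout are 41 × 0.8 = 32.8, about 33 per group.
- Assumed, because the article gives no figure: the share q of exposed women with an earlier course, 10–35%, and the relative drop e in milk IgA from such a course, 10–20%. The illustration also assumes that the early effect adds to any late effect.

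**Step 4: shift in the group difference**, b = q × e × 3.8 g/L.

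- Low end: 0.10 × 0.10 × 3.8 = 0.038 g/L; 0.038 / 0.76 = 5%.
- High end: 0.35 × 0.20 × 3.8 = 0.266 g/L; 0.266 / 0.76 = 35%.

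Out of 41 exposed women, these shares are about 4 (41 × 0.10 = 4.1) to 14 (41 × 0.35 = 14.4).

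**Step 5: rejection rate if late exposure had no effect.** This is the power of a two-sided, two-sample t-test at standardised difference b / 1.

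| q | e | Shift (g/L) | 33 per group | 41 per group |
|---|---|---|---|---|
| 10% | 10% | 0.038 | 0.053 | 0.053 |
| 25% | 10% | 0.095 | 0.067 | 0.071 |
| 25% | 20% | 0.190 | 0.118 | 0.136 |
| 35% | 20% | 0.266 | 0.186 | 0.221 |

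The range is about 5–22%. At the low end the nominal 5% level is practically unchanged.

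**Step 6: room to tighten eligibility instead.** At the stated 1.5 women per week, 1.5 × 52 = 78 candidates arise per year, and 41 / 78 = 53% must be eligible and consent. If 25–35% were removed for an earlier course, 78 × 0.75 = 58.5 to 78 × 0.65 = 50.7 would remain, and the required yield becomes 41 / 58.5 = 70% to 41 / 50.7 = 81%.

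**The case against.** **A never-exposed comparator is a legitimate choice.** The study calls itself a proof-of-concept mechanistic study, and much of the Abstract and Discussion speaks of prenatal antibiotics in general. This stands. For prenatal antibiotics against none, earlier courses in exposed women are part of the exposure and do no harm. What remains is the narrower claim about timing in the Introduction.

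**The size cannot be taken from the article.** A reader might infer from the Abstract's 25–35% that 10–14 of the 41 exposed women will have had an earlier course. The documents do not support that. The figure is an upper bound and covers the whole pregnancy, including the third trimester; it is not a share treated before 32 weeks. If the exclusion means any short course, fewer still would qualify. The 10–20% drop in IgA also has no source in the article: the animal data it describes concern the last week of pregnancy, and the upper value equals the entire difference the study is designed to detect. The numbers above can only illustrate.

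**The full protocol or SAP may deal with earlier courses.** It may, and a missing adjustment in a condensed article is not held against it here. The eligibility rules, however, are stated in the article, and they create the imbalance whatever the analysis.

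**Conclusion.** The concern holds in a limited form. As written, the criteria compare late exposure, with or without earlier exposure, with no exposure at any time in pregnancy. A difference in milk or fecal IgA therefore cannot be attributed cleanly to antibiotics given shortly before birth.

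A reader might go further and conclude that earlier courses do occur in the exposed group and will be credited to late exposure. The documents support only that they can occur there; how many there will be is not stated.

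The size is likewise unknown. On the assumed ranges the distortion runs from negligible to about a third of the target difference, and the false-positive rate for a late effect from the nominal level to about 22%. Both rest on the assumed share, effect and additivity.

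**What to change.** 1. Record from the obstetric chart every systemic antibiotic course before 32 weeks in exposed women.
2. Prespecify that the milk and fecal IgA comparisons are repeated without exposed women who had such a course.
3. State whether the exclusion for treatment shorter than 7 days refers to the index course.

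The cost is one chart field, one clarified phrase and a less precise repeat comparison. If 4 to 14 of 41 exposed women were set aside and all 41 controls kept, the standard error (SD 1) would rise from √(2/41) = 0.221 to √(1/41 + 1/37) = 0.227 or √(1/41 + 1/27) = 0.248 g/L, that is, by about 3–12%. No participant is lost from the main analysis.

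Limiting exposed eligibility to women with no earlier course would remove the imbalance at source, but it is an option only if recruitment allows. If 25–35% of candidates were lost, about 70–81% of the rest would have to meet the other criteria and consent, against 53% now, which could threaten the stated one-year feasibility.

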### Laboratory methodologies

Breast milk will be manually expressed by trained nurses or by the mothers themselves after cleansing of the breast skin. Feces will be collected from the diaper using a sterile plastic spatula. All biological samples will be collected in sterile containers and immediately frozen at −80 °C (samples collected during hospital stay and study visits), or at −20 °C for samples collected at home (neonatal feces during follow up) and subsequently transferred at −80 °C. This will allow to minimize alterations of IgA pool and microbiota composition. For experimental analysis samples will be defrosted in batches, always with an equal number of samples between experimental groups.

IgA quantification in breast milk will be performed with commercially available ELISA kit (Invitrogen, cat. BMS2096), in technical duplicates and including a standard curve in each 96-well plate. Breast milk samples will be devoid of fat components by centrifugation and appropriately diluted in assay diluent. Feces will be defrosted, suspended in PBS with 0.1 mg/ml of trypsin inhibitor from soybean (Sigma Aldrich) at a concentration of 100 mg/ml, and homogenized through shaking at 30 Hz for 20 s in a tissue lyser (Qiagen), after the addition of 1.4 mM ceramic beads (MP Biomedicals). Then they will be centrifuged at 50 × *g* for 10 min to remove debris, and supernatant will be diluted 1:5 with assay diluent.

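### The first sample may be taken on any day of the first week, and neither the matching nor the named tests account for sampling day; if milk IgA changes over that week, unequal timing would bias the first-week comparison

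*Protocol article*

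**What the plan says.** All references are to the Protocol article.

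- **Time points** (Study design, text after the Fig. 1 caption). IgA, microbiota, IgA-coated bacteria and CCL28 are measured "at the following time points:during the first week of lifeat 1 month of lifeat 3 months of life", then once more at 8–12 months or when breastfeeding stops. No day or sub-window within the first week is given.
- **Matching** (same section). "Case-control dyads will be matched for gestational age at delivery and at the start of antimicrobial treatment". Postnatal day of sampling is not listed.
- **Sample collection** (Laboratory methodologies). Samples are "immediately frozen at −80 °C (samples collected during hospital stay and study visits"; the only home samples mentioned are infant stools during follow-up. Thawing is in batches balanced by group.
- **Sample size** (Data collection, sample size and statistical analysis). "Considered an average content of IgA of 3.8 g/L (S.D. ± 1 g/L" is the basis, with no day of lactation attached. The power statement reads "around 34 women per group would be enough to detect a prudential difference of 20% with a power of 0.9 and an Alpha equal to" (the level given there is 5%). The animal-based expectation is larger: "an average drop of approximately 30% in breast milk IgA can be expected after prenatal ABX treatment".
- **Tests** (same section). "Mann-Whitney two-sided unpaired U-test, for non-normally distributed data (visually checked), or two-sided unpaired" t-test for two groups, and repeated-measures ANOVA for measurements over time. No covariate is named.
- **Hypothesis** (Introduction). Antibiotics late in pregnancy "can reduce the absolute amount and the polyreactivity of breast milk IgA after birth".

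**The concern.** The first-week sample is the one nearest to the prenatal exposure, so it is a natural place to look for the milk effect. If milk IgA changes with day of lactation during that week, samples taken early and late in the window are not comparable, yet they share one visit label.

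The groups are not randomised. Exposed women are those with ruptured membranes, preterm labor, chorioamnionitis, pneumonia or similar conditions. These could plausibly change the length of stay or the time at which milk is first expressed, and hence the day of sampling. Nothing in the schedule, matching or tests as stated would prevent or correct such a difference. Balanced thawing controls the laboratory batch, not the postnatal day.

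Two consequences are possible and should be kept apart. A systematic difference in sampling day biases the first-week comparison. Scatter in sampling day that is equal in both groups causes no bias but adds variance.

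**Working it through.** **Inputs from the article.** Mean 3.8 g/L, SD 1 g/L, difference sought 20% = 0.76 g/L, alpha 0.05, two-sided unpaired test, 34 evaluable per group, 41 enrolled per group, 20% dropout.

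**Assumptions (not in the article).** Milk IgA falls by a constant fraction r per day within the first week, with r from 2% to 25%. The mean sampling day differs by k = 1 or 2 days between groups.

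**1. The article's own figure.** n per group = 2(1.960 + 1.282)² × 1² / 0.76² ≈ 37 (38 by t-test), not 34. With 34 per group, power is 0.88 (normal) or 0.87 (t-test). That gap is a separate matter; it is given here only as the baseline.

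**2. Bias from a systematic shift.** False difference = 1 − (1 − r)^k.

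| Fall per day | 1-day shift | 2-day shift |
|---|---|---|
| 2% | 2% | 4% |
| 5% | 5% | 10% |
| 10% | 10% | 19% |
| 15% | 15% | 28% |
| 20% | 20% | 36% |
| 25% | 25% | 44% |

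A bias equal to the full 20% requires (1 − r)^k = 0.8. That is r = 20% per day for 1 day, and r = 1 − √0.8 = 10.6% per day for 2 days.

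**3. Effect on the test at 34 per group, SD 1 g/L (normal approximation).** The smallest significant observed difference is 1.960 × √(2/34) = 0.475 g/L, which is 12.5% of 3.8. The left pair of columns assumes no true effect. The right pair assumes a true 20% drop with controls sampled later; power without a shift is 88%.

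| Fall per day | Chance of p < 0.05, 1 day | 2 days | Power, 1 day | 2 days |
|---|---|---|---|---|
| 2% | 6% | 10% | 81% | 71% |
| 5% | 12% | 33% | 65% | 36% |
| 10% | 35% | 85% | 35% | 4% |
| 15% | 65% | 99% | 12% | <1% |
| 20% | 88% | 100% | 2.5% | <1% |

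**4. Scatter without imbalance.** Take sampling days spread evenly over days 1–7 in both groups (SD 2 days). On the log scale the baseline SD is √ln(1 + (1/3.8)²) = 0.259, the timing SD is −ln(1 − r) × 2, and the two add in quadrature. The effect is |ln 0.8| = 0.223. Evaluable n is 41 × 0.8 = 32.8, taken as 33 per group, with a two-sided t-test.

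| Fall per day | Timing SD | Combined log-SD | Power |
|---|---|---|---|
| none | 0 | 0.26 | 0.93 |
| 5% | 0.10 | 0.28 | 0.89 |
| 10% | 0.21 | 0.33 | 0.76 |
| 15% | 0.33 | 0.42 | 0.58 |
| 25% | 0.58 | 0.63 | 0.29 |

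On the g/L scale with 34 per group the pattern is the same: power goes from 88% to 83% at 5% per day, 69% at 10% and 37% at 20%.

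**The case against.** **The article is condensed.** It refers to pre-planned visits and to a figure that is not shown, and visit windows, recorded sample times and covariates often sit in a full protocol or analysis plan. This is fair as far as missing detail goes. It does not remove the point, because the article does state a window, and that window is a whole week.

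**The even 1–7 day spread is near the worst case.** The Laboratory methodologies section suggests that the first milk sample is taken during the hospital stay, which would narrow the real spread. The stated SD of 1 g/L may also already include timing variation. Both points stand, so the power losses in step 4 are closer to an upper bound than to a forecast. The row at 25% per day implies a fall of 82% between day 1 and day 7 (1 − 0.75^6), which is extreme.

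**Imbalance is inferred.** The article reports no difference in sampling day between groups. Matching on gestational age at delivery, excluding births before 34 weeks and excluding infants given antibiotics in the first week all limit likely sources of one. This stands too: imbalance is possible, not shown.

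**Stronger readings.** A reader might infer that first-week timing is bound to mimic or hide the 20% effect, because milk IgA and newborn stool change fastest then. The article says nothing about how fast either changes, so that rests on outside knowledge. A reader might also infer that the study's powered comparison is compromised. The article does not link 3.8 g/L or the 20% to the first-week sample, and three later time points exist. No effect size is given for stool IgA, CCL28 or microbiota, so nothing can be quantified for them.

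**Conclusion.** The point holds in conditional form. As stated, the first-week window leaves postnatal day of sampling free, and neither the matching nor the named tests compensate. If milk IgA falls by 2–25% per day in that week (assumption), a systematic 1-day difference between groups produces a false difference of 2–25%, and a 2-day difference 4–44%. Only falls of about 20% per day (1 day) or 10.6% per day (2 days) would match the full 20%. Smaller ones still matter: at 5% per day the bias is at most about half the effect sought, yet the false-positive chance is 12% to 33%. At 2% per day the false-positive chance is 6% to 10%.

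Equal scatter in both groups lowers power without bias: from 0.93 to 0.89 at 5% per day and 0.76 at 10%, under a near worst-case spread and only if the stated SD does not already contain it. The scope is the first-week comparison. The concern reaches the sample-size calculation only if that visit is the one it was meant for.

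**What to change.** 1. Replace the whole-week window with one narrower postnatal sampling window, the same in both groups. The sponsor should choose it to fit the hospital stay; the article gives no basis for a particular hour or day.
2. Record hours since birth for every first-week sample. If this is not recorded at collection, it may not be recoverable later.
3. Where possible, sample each control on the same postnatal day as its matched exposed dyad.
4. Include hours since birth as a covariate in the first-week comparison. Any practical window still has some width, so the covariate is needed as well as the window.

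The cost is one line in the visit schedule, one recorded time per sample and one model term. Some samples will miss the window; they should be kept and analysed with their actual time as covariate.
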